## Discussion

In this study, we have described the protocol for the planned development and validation of a new clinical prediction model for the decline of renal function in Caucasian people with DM2 to aid decision-making in clinical care. Our methodological approach will be based on a multivariable linear mixed model able to account for the dependence of clinical parameters per subject over time and for the similarity of individuals within the same country. Previous studies have employed risk prediction based on (multinomial) logistic regression models for which as a dependent variable the dichotomized eGFR slope was used, after estimation by least squares using the repeated measurements and then partitioning at arbitrary cutpoints. Each eGFR strata then covers different intervals on the eGFR slope spectrum and is supposedly indicative of varying severity of the progression of renal function loss. However, this approach suffers from several shortcomings. First, individual eGFR slopes can only be estimated very inaccurately, as only very few data points at non-equidistant time points are available for each patient [5]. Moreover, the categorization of the resulting eGFR slopes adds another layer of possible bias as it leads to subjects close on the continuous spectrum but on the opposite sides of the cutpoint being characterized as different [31]. By contrast, our approach avoids the issues associated with the imprecise estimation of slopes and inappropriate dichotomization prior to model development and takes the observed data fully into consideration when estimating the parameters of the model. In addition, we include the baseline measurements of eGFR into the outcome vector of an individual, as it is subject to the same measurement error as later eGFR measurements. In this way, these baseline measurements contribute to a more precise estimation of the error variance. Nevertheless, available eGFR measurements at the time of prediction (application of the model) can still be incorporated in our approach to optimize the predicted eGFR trajectory. In addition, the clustered data structure due to the two multicentre cohorts (GCKD and PROVALID) for model training will be taken into account by including an additional random intercept for the country in contrast to existing models. Therefore, the potential heterogeneity of model performance across the countries, which are distinct between GCKD and PROVALID, is prevented and hence, the generalizability to unseen individuals is improved.

However, this study will have a few limitations. First, it is to be expected that for some individuals not all creatinine measurements will be available, in particular, at later time points. Such random missingness is common in prospective longitudinal studies. Even in the case of informative missingness, by capturing much information about the patients by means of domain-expertise-selected clinical baseline variables, which are included in multivariable modeling, the mixed model is still able to provide unbiased predictions. Second, we will not include extensive biosampling data (e.g., metabolomics, proteomics, lipidomics) in the model. The inclusion of these biomarkers may improve the predictive accuracy of the model, but the scientific evidence for an added value in prediction is still scarce and the biomarkers have no validated test characteristics. We will rather prioritize clinical variables that are regularly collected and which are widely available to ensure the broad applicability of our model. Lastly, the lack of standardization of creatinine assays across cohorts inflicts variability of the clinical laboratory serum creatinine measurements and hence can induce potential bias in calculating eGFR.

The key strength of this study includes not only the refined methodology in the development of the prediction model, but also its large sample size due to the usage of two prospective observational cohort studies PROVALID and GCKD for model development. This ensures stable parameter estimation of the model. Another strength is the availability of an additional, independent prospective cohort study, DIACORE, for external validation after model development. To our knowledge, this is the first prediction model specifically developed for a central European population suffering from DM2 and covering a wide range of CKD stages.

Overall, we have outlined a robustly developed and validated clinical prediction model which will generalise to a wide range of patients with regard to initial CKD progression suffering from DM2. It will also be derived from a diverse and multinational population using two large studies and will be used to predict deterioration in renal function in DM2 patients to improve further eGFR development through early intervention in patients at high risk for the rapid progression of renal decline.

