### Objective

The main objective of the planned analysis is the development, internal-external, and external validation of a personalized prediction model for eGFR loss per year in Caucasian people with DM2. It is based on clinical information and laboratory measurements recorded at baseline. A secondary aim is the implementation of the externally validated prediction model as a publicly available web application to facilitate general applicability in clinical care based on data from recent eras using modern therapy.

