#### GCKD—German chronic kidney disease

The prospective cohort study GCKD consists of around 5000 people with CKD. Patients aged 18–74 years and suffering from CKD were included in case of an eGFR between 30 and 60 ml/min/1.73m^2^ with or without urinary albumin excretion (CKD KDIGO Stage 3) or a better preserved eGFR in the presence of urinary albumin excretion >300 or protein excretion >500mg/day, and were followed up to 10 years. For the full inclusion and exclusion criteria of patients, see Table 1. Out of the 5000 recruited individuals, 1800 had diabetes and therefore represent the relevant patient subset for the prediction model in this work. The follow-up visits were set up in bi-yearly intervals. The main objective of the GCKD study cohort was to identify and validate risk factors for CKD, end-stage renal disease (ESRD), and cardiovascular disease (CVD) events.

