### Prediction model development

People adhering to the inclusion and exclusion criteria from either the PROVALID or GCKD study will be considered for model building. Mixed-effects modeling accounts for the dependencies between repeated measurements per person over time and the similarity among people belonging to the same study cohort, hence they are commonly employed to analyze longitudinal and clustered data. Here, we will consider hierarchically nested random effects for the country and people within a country, such that the heterogeneity of eGFR trajectories between the five countries within the development cohort can be modeled appropriately [26]. More specifically, we will use random effects for the intercept and the slope of the repeated eGFR measurements over time and an additional random intercept for the country. We will include the baseline eGFR value in the outcome vector to provide more stable estimates of variability. When applying the model, any available eGFR measurements of an individual for whom eGFR trajectory predictions should be obtained can be used to improve predictions. A similar approach has been conducted by Selles et al. [27] to develop a prediction model not only able to deal with multiple measurements per subject but also able to allow these repeated clinical measurements to contribute to the prediction of an unseen individual. The set of clinical variables outlined in Table 2 will constitute the fixed effects. Automated variable selection will not be conducted as the set of predictors was chosen by background knowledge. Furthermore, due to the large sample size available for estimation overfitting is expected to be minimal, such that further regularization of the predictor effects will be omitted. Clinically relevant pairwise interactions of the independent variables with time will be investigated and added if their inclusion improves the prediction accuracy of the model as determined by the Akaike information criterion (AIC). Any model misspecification, e.g., regarding functional forms of the variables in the model, will be assessed using a plot of the marginal residuals versus the individual variables. Variables with non-linear relationships with the outcome as exhibited by these residual plots will then be modeled using restricted cubic splines to improve the model fit [28]. In addition, the relevance of the inclusion of such non-linear terms for improving the model fit will be evaluated in terms of the AIC.

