More formally, the model for the continuous eGFR values *Y*_*it*_ at time point *t* (*t* = 0, …, *T*) for subject *i* (*i* = 1, …, *n*) is defined by
1$$ {\mathrm{Y}}_{\mathrm{i}\mathrm{t}}={\upbeta}_0+{\mathrm{a}}_{\mathrm{i}}+{\upbeta}_1X+{\upbeta}_2\mathrm{t}+{\upbeta}_3\mathrm{tX}+{\mathrm{b}}_{0\mathrm{i}}+{\mathrm{b}}_{1\mathrm{i}}\mathrm{t}+{\upepsilon}_{\mathrm{i}\mathrm{t}}, $$

with normally distributed residuals $$ {\epsilon}_{it}\sim N\left(0,{\sigma}_{\epsilon}^2\right) $$ with mean 0 and variance $$ {\sigma}_{\epsilon}^2 $$, random country-specific intercepts assumed to be *a*_*i*_~*N*(0, *τ*^2^), the random coefficients (*b*_0*i*_, *b*_1*i*_)~*MN*(0, *G*) (where MN denotes the bivariate normal distribution with an unspecified covariance matrix G, defined by the diagonal elements $$ {\upsigma}_0^2 $$ and $$ {\upsigma}_1^2 $$ and the off-diagonal σ_01_) and the vector of regression coefficients for the clinical independent variables *β* = (*β*_0_, *β*_1_, *β*_2_, *β*_3_). It should be noted that for simplicity of description, we here consider a single clinical predictor variable *X*, where *β*_1_ and *β*_3_ represent the regression coefficients corresponding to the clinical predictor variable and its interaction with time. Without loss of generality, more clinical predictors can be added, each with two regression coefficients for the baseline effects of the predictor and the corresponding interaction with time. When considering restricted cubic splines for a variable, this variable will be represented by several corresponding basis functions in (1).

Model (1) allows to prognosticate baseline and follow-up values of eGFR for a new person *j* given the value of the clinical predictor *X*, assuming that for that new person the random intercept and slope are equal to their expected values of 0. Further, we will assume the expected random country effect of *a*_*j*_ = 0 for the prediction of eGFR in a new individual. In order to incorporate a baseline eGFR measurement *y*_*j*0_ into the prediction, a best linear unbiased predictor (BLUP) of the individual’s random effects can be obtained through the posterior distribution of the random effects. The random intercept for that new subject *j* is then estimated by
2$$ {\hat{\mathrm{b}}}_{0\mathrm{j}}=\frac{\upsigma_0^2\left({\mathrm{y}}_{\mathrm{j}0}-{\hat{\mathrm{y}}}_{\mathrm{j}0}\right)}{\upsigma_0^2+{\upsigma}_{\upvarepsilon}^2}, $$

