### Model evaluation, performance, and external validation

An analysis of the conditional residuals will be conducted to check correct model specification, e.g., normality, linearity, and homoscedasticity of the error terms. Next, the importance of each independent variable will also be evaluated by the drop in the adjusted *R*^2^, i.e., the loss in estimated explained variation when the respective predictor is removed from the model.

The performance of the prediction model will be evaluated by an internal-external validation procedure to obtain a reliable assessment of its generalizability of prediction to unseen data [29]. The unit for the non-random data splitting will be the six countries within the PROVALID and GCKD studies (GCKD: Germany; PROVALID: Austria, Hungary, Netherlands, Poland, and Scotland) such that for each iteration, one regional group with its study participants are withheld from model training and then used for testing.

The prediction performance will further be assessed through:
Discrimination in terms of Kendall-tau-b concordance correlation coefficients at each time point, i.e., the concordance of the predicted eGFR values at time *t* obtained by Eq. (4) and the actual observed eGFR in each pair of patientsCalibration in terms of the slope of the calibration curve by
I.Regressing the predicted eGFR on the actual eGFR values at each time pointII.Plotting the estimated mean risk for fast progression per decile against the observed ratio of fast progression within each risk decileExplained variation in terms of adjusted *R*^2^, i.e., the proportion of explained variability in the outcome by the independent variables

The external validity of the model will be examined by applying the final prediction model to the DIACORE study cohort and evaluating the three performance measures outlined above.

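### A random country intercept, set to zero for every new person, cannot prevent between-country heterogeneity in predicted annual eGFR loss; it should be measured and reported instead

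*Protocol article*

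**What the plan says.** The target of the work is a "personalized prediction model for eGFR loss per year in Caucasian people with DM2" (Objective), which is a slope.

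Under Prediction model development, the random part of the model is "random effects for the intercept and the slope of the repeated eGFR measurements over time and an additional random intercept for the country". Country therefore has an intercept and no slope. The same section says that in this way "the heterogeneity of eGFR trajectories between the five countries within the development cohort can be modeled appropriately". For a new individual it continues "we will assume the expected random country effect of" zero.

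Under Model evaluation, performance, and external validation, the count differs: "The unit for the non-random data splitting will be the six countries within the PROVALID and GCKD studies". The list there assigns Germany to GCKD and the other five countries to PROVALID.

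On GCKD itself: "Out of the 5000 recruited individuals, 1800 had diabetes and therefore represent the relevant patient subset". Entry to GCKD required an eGFR of 30 to 60, or a higher eGFR together with albuminuria or proteinuria. PROVALID did not select on CKD.

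The Discussion concludes from the country intercept that "the potential heterogeneity of model performance across the countries, which are distinct between GCKD and PROVALID, is prevented" and that generalizability is thereby improved.

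**The concern.** The Discussion states as a property of the model something that its equations do not provide. A reader or a user of the web tool could take it that annual eGFR loss is predicted equally well in every country, when the model has no term through which countries could differ in annual loss.

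A second issue sits underneath. In the development data, country and cohort cannot be separated for Germany. GCKD is selected jointly on baseline eGFR, which is part of the outcome vector, and on albuminuria, which is closely tied to the predictor UACR. A shift in mean level cannot absorb that kind of selection. DIACORE is also German but was not recruited on eGFR. The Introduction also offers predictions for people who have no baseline eGFR, and these rest entirely on the fixed effects and the zero country level.

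**Working it through.** The plan gives no figure for this point. Its sample sizes (271, 3048, 1569 and 903 for 13 predictors) reproduce exactly but do not bear on it.

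**1. The country term and the slope.** Eq. (1) is Y = β0 + a + β1X + β2t + β3tX + b0 + b1t + ε. Differentiating in t gives β2 + β3X + b1, which is the plan's own predicted slope. The term a has gone, and it would be gone even if a new person's country effect were known. Eq. (5) uses only this slope and its variance.

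**2. Eq. (2) and the country variance τ².** Let r be observed minus predicted baseline eGFR. The plan uses b0 = σ0² r/(σ0² + σε²) and, from Eq. (3), b1 = σ01 r/(σ0² + σε²). Under Eq. (1) the variance of r for a person from an unseen country is τ² + σ0² + σε². The predictors are then:
- a = τ² r/(τ² + σ0² + σε²)
- b0 = σ0² r/(τ² + σ0² + σε²)
- b1 = σ01 r/(τ² + σ0² + σε²)

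Without τ², the country deviation is credited to b0 and part of it passes into the slope. Illustration with assumed inputs:
- σ0² = 21.4² − (3 × 1.5)² − 6² = 401.7, so σ0 = 20.0. This takes the SD of 21.4 from Sample size, a UACR effect of -3 per log unit, a log-UACR SD of 1.5 and a residual SD of 6.
- σ01 = 0.2 × 20.0 × 1 = 4.0 (slope SD 1, correlation 0.2).
- τ² = 26²/6 = 112.7 (one country at -26, see step 4, and five at 0).

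For r = 10:

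| | Plan | With τ² |
|---|---|---|
| Level update | 9.18 | 9.35 |
| Slope update per year | 0.092 | 0.073 |

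The omission is an error of form with a small effect here. Without a baseline eGFR, the predictive SD at baseline goes from √437.7 = 20.9 to √550.4 = 23.5, about 12% wider.

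**3. Unmodelled country slopes.** Take a predicted slope of -2 and the default cutpoint of -3, with an assumed slope SD s. Then Pr(slope < -3) = Φ((-3 − (-2 + u))/s), where u is the country's unexplained slope difference.

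| s | u = -0.5 | u = 0 (as stated to the user) | u = +0.5 |
|---|---|---|---|
| 1.0 | 0.31 | 0.16 | 0.07 |
| 1.5 | 0.37 | 0.25 | 0.16 |
| 2.0 | 0.40 | 0.31 | 0.23 |

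The documents give no value for u.

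**4. GCKD-type selection.** Simulated with eGFR mean 78.4 and SD 21.4, an assumed UACR effect of -3 per log unit, assumed median UACR 15 and log-SD 1.5, the GCKD entry rule, a ratio of 1800:4000, and no true country difference. The fitted UACR effect was -2.8 in PROVALID, +2.1 within GCKD and -1.1 pooled with separate intercepts. A false German offset of -26 appeared. Averaged over six countries that is -26/6 = -4.3.

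Predictions for an unselected, DIACORE-like sample (five yearly visits, 4 replicates) were:

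| Prediction | Pooled fit | PROVALID-only fit |
|---|---|---|
| Year 4, Eq. (4), bias | -0.36 to 0.15 | -0.30 to 0.17 |
| Year 4, Eq. (4), RMSE | 9.26 to 9.39 | 9.27 to 9.39 |
| Annual slope, bias | 0.03 to 0.13 | -0.07 to 0.02 |
| No baseline eGFR, RMSE | about 22.0 | about 21.5 |

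Bias of the pooled fit without a baseline eGFR was about -4.

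**5. Sensitivity.** A separately built simulation, with one predictor explaining 5% to 30% of variance, found the pooled baseline effect attenuated by 19% to 78%. The false German offset there was -12 to -13. The time effect moved by at most about 0.15 and the interaction with time by at most about 0.07. Over 27 further scenarios the pooled UACR effect was always attenuated, by at least 29%, and the false offset ranged from -17 to -29.

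**The case against.** The strongest reply is that the harm from selection largely disappears in the predictions the plan actually scores. Concordance is assessed on Eq. (4) predictions, which use baseline eGFR; DIACORE is judged by the same measures, and the web tool asks for eGFR. Step 4 bears this out, so this part stands and limits the point.

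It is also fair that the country intercept is not idle. In fitting, it separates τ² from σ0² and so feeds Eqs. (2) and (3). Setting it to zero for a new person is an openly stated convention. Slope differences due to measured predictors can enter through the interactions with time, so only the remainder is unmodelled.

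Leave-one-country-out validation is already planned, and the fold without Germany is a PROVALID-only fit. This measures heterogeneity, though. It does not prevent it, and so does not rescue the Discussion sentence.

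A reader might infer that pooling GCKD with PROVALID materially biases predicted annual loss. An assumed slope difference of 1 mL/min/1.73m² per year between cohorts, with a GCKD information share of 0.32, would put the common slope off by 0.32 per year for PROVALID-type and 0.68 for GCKD-type patients. The documents give no such difference, and selection alone moved the slope terms little.

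**Conclusion.** The point holds as a mismatch between claim and model. That the intercept cannot prevent heterogeneity in annual eGFR loss follows from the plan's own equations and needs no assumption. The omission of τ² from Eq. (2) is likewise algebra, with a small effect in the illustration. The conflict between five and six countries is plain in the text.

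The selection effect is an inference. Its direction was consistent across the scenarios tried, but its size rests on assumed UACR distributions and effects and on few replicates. Under those inputs it costs about -4 mL/min/1.73m² in predictions without a baseline eGFR and little elsewhere.

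A reader might also conclude that the model must be rebuilt with a cohort-by-UACR term and all predictions made at the PROVALID level. The documents do not require that. Such terms cannot be estimated when Germany is held out, and they would reduce what GCKD contributes to covering a wide range of CKD stages.

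**What to change.** 1. In the Discussion, replace the claim of prevention. Say that the country intercept accounts for level differences in fitting, and that heterogeneity will be quantified by calibration intercept and slope, including for annual eGFR loss, for each held-out country, with their between-country spread.
2. As sensitivity analyses, fit a cohort-by-time term or a country random slope, and a PROVALID-only model. Keep the added term if it improves AIC or calibration.
3. Include τ² in Eq. (2) and in the prediction intervals. The predicted country effect from step 2 of the working must then be added in Eq. (4); enlarging the denominator alone would shrink the level too far.
4. State that predictions without a baseline eGFR are exposed to GCKD selection, and evaluate them separately in DIACORE.
5. Correct five to six countries under Prediction model development.

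The cost is a few coefficients and extra tables. Variance components from six countries are imprecise. Intervals become slightly wider when a baseline eGFR is given, and about 12% wider at baseline without one under the inputs above. A cohort-by-time term cannot be estimated in the fold without Germany, and if kept, the plan must say at which cohort level a new person is predicted.

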### Target population

The following inclusion criteria will be applied to the individuals from the PROVALID, GCKD, and DIACORE studies for the development and validation of the prediction model in this work:
Caucasian ethnicityPresence of DM2 at baselineeGFR > 30 mL/min/1.73m^2^ at baselineAged 18–75 years at baselineAt least three visits with recorded serum creatinine measurements (including baseline)At least 2 years of follow-up

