### Statistical analysis

Patient’s baseline characteristics will be described for the study cohorts separately, using mean and standard deviation for continuous variables, or median and interquartile range in case of non-normality, and absolute and relative frequencies for categorical variables. Skewed variables will be transformed by the logarithm before the analysis. Data availability and the fraction of missingness will be assessed and reported for each variable. As the fraction of missing data is expected to be low, a complete case analysis will be carried out. Data screening through the computation of sample characteristics and visual inspections to identify the presence of missing values, skewed variable distributions, and outliers, as well as reporting of conducted screening activities will adhere to the conceptual framework for initial data analysis by Huebner et al. [25]. All analysis will be performed with the software R version 4.0.2.

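### The claim that baseline covariates keep the mixed model unbiased under informative missingness is wrong as written; it holds only under missing at random

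*Protocol article*

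**What the plan says.** The Discussion expects that for some people "not all creatinine measurements will be available, in particular, at later time points". It labels this loss as random: "Such random missingness is common in prospective longitudinal studies". It then goes further: "Even in the case of informative missingness, by capturing much information about the patients by means of domain-expertise-selected clinical baseline variables", and, because these variables are in the multivariable model, "the mixed model is still able to provide unbiased predictions".

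The Methods sections neither qualify nor support that statement:

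- **Statistical analysis:** "As the fraction of missing data is expected to be low, a complete case analysis will be carried out". No expected fraction is given.
- **Target population:** at least three creatinine visits and "At least 2 years of follow-up" are required in all three cohorts, including the external validation cohort DIACORE.
- **Prediction model development:** each person has a random intercept and a random slope, and each country a further random intercept. The fit uses lme(). JMbayes is named only for the function that updates an individual's prediction, so the model described has no component for time to exit.

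**The concern.** The sentence asserts a statistical property that the model does not have. Missingness is informative when, after conditioning on everything modelled and observed, it still depends on values that were not observed. If the baseline variables remove that dependence, the missingness is ignorable and no longer informative. If they do not, the model is not protected. Under either reading the sentence as written is wrong.

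The direction of a possible error bears on the purpose of the tool, which is to pick out people at high risk of rapid decline and to report predicted eGFR at 1–5 years. If people with steeper unobserved decline leave sooner, the fitted average decline is too shallow and the between-person spread too small. The predicted risk of rapid decline is then too low.

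Validation would not by itself show this. The same follow-up rules select the DIACORE sample, and performance is judged against eGFR values that were actually observed.

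**Working it through.** The challenged sentence carries no figure, so there is nothing in it to reproduce. The check has two parts.

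**1. What the model needs.** In model (1), the slope of person i is β₂ + β₃X + b₁ᵢ, with b₁ᵢ of variance σ₁². The likelihood is valid without a model for exit if

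P(exit | X, observed eGFR, unobserved eGFR) = P(exit | X, observed eGFR).

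Baseline covariates need not explain the slope completely. Exit need only be unrelated to the rest of the trajectory once X and the observed eGFR are known. If exit still depends on b₁ᵢ after that conditioning, equality fails, and putting X in the model does not restore it.

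**2. How much it could matter.** From the documents: mean eGFR 78.4, the default cutpoint of −3 per year, and the three-visit rule. All slope and exit parameters below are assumptions, because the documents give none. Data were simulated from random-intercept, random-slope models and refitted by maximum likelihood. The probability of rapid decline is Φ((−3 − mean slope)/slope SD).

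*Setting A (assumed).* True mean slope −1.80 and slope SD 2.0. Exit is 5% per year at the average slope, rising 1.65-fold or 2.7-fold per SD of steeper slope. This gives about 24–32% exit over 5–6 years.

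- True probability: Φ((−3 + 1.80)/2.0) = Φ(−0.60) = 27%.
- Annual visits: fitted slope −1.63 (1.65-fold) or −1.42 (2.7-fold).
- Two-yearly visits: −1.60 or −1.34.
- Slope SD falls to between 1.95 and 1.79.
- Mildest case: Φ((−3 + 1.63)/1.95) = Φ(−0.70) = 24%.
- Strongest case: Φ((−3 + 1.34)/1.79) = Φ(−0.93) = 18%.
- Refitted with a baseline covariate in the model, with and without the three-visit rule: slopes −1.63 to −1.32, probabilities 24% to 17%.
- Relative error in the slope: (1.80 − 1.63)/1.80 = 9% to (1.80 − 1.32)/1.80 = 27%.

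*Setting B (assumed), contrasting mechanisms.* True mean slope −2.00, slope SD 2, intercept SD 18, residual SD 6, intercept–slope correlation 0.2. Visits are annual to year 5, one baseline predictor is in the model, and the three-visit rule is applied. True probability: Φ(−0.50) = 0.309.

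| Exit depends on | Exit by year 5 | Fitted slope | P(slope < −3) |
|---|---|---|---|
| Baseline predictor | 9% / 20% / 41% | −2.00 / −2.00 / −2.01 | 0.309 / 0.309 / 0.310 |
| Previously observed eGFR | 8% / 19% / 41% | −2.00 / −1.99 / −1.96 | 0.308 / 0.307 / 0.302 |
| Latent slope (informative) | 11% / 22% / 42% | −1.87 / −1.70 / −1.41 | 0.279 / 0.243 / 0.187 |

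The first two mechanisms leave the fit essentially unbiased. Under the third, the probability is understated by 3, 7 and 12 percentage points, although the baseline predictor is in the model throughout.

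**The case against.** Five points can be made for the plan.

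- **Terminology.** The authors may mean that loss which looks informative marginally becomes ignorable after rich conditioning. That is a sensible hope, but it is the missing-at-random assumption and should be stated as one. A non-zero random slope does not contradict it, so the model's own random slope does not show that the assumption fails.
- **Kidney failure is not automatically informative.** Renal replacement follows low eGFR, which repeated visits largely record, so part of that exit is close to missing at random. It may also be uncommon: with mean 78.4, SD 21.4, baseline above 30, the slopes of setting A and an assumed threshold of 15, only about 0.4% would fall below it by year 5. For an assumed uniform baseline of 30–60 the figure is about 6%. Exit on the simulated scale would have to come mainly from death or other drop-out, for which the documents give no rates. This stands.
- **The strong scenario is strong.** At two SD steeper than average, 5% × 2.7² is about 36% exit per year. The plan expects missing data to be low, and at 11% exit the understatement is 3 points. This also stands.
- **The simulated probability is not the tool's output.** It describes the slope distribution at an average predictor value. The web tool's probability is individual and also conditions on baseline eGFR, and the simulation used one predictor rather than 13. The figures show direction and rough scale only.
- **A sensitivity analysis may sit elsewhere.** A reader might infer that death and kidney failure are left wholly unexamined. The article condenses a fuller plan that is not shown, so its silence does not support that. The sentence in the Discussion still needs correcting.

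**Conclusion.** The statement is wrong as written and should be corrected. Baseline covariates give valid inference here only if, together with the observed eGFR values, they make the missingness ignorable.

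If exit still depends on the residual slope, the error runs towards too shallow a mean decline, too small a slope spread and too low a risk of rapid decline. Under the assumed exit of about 24–32%, the understatement is roughly 3 to 10 percentage points on a true 27%. With lower exit it is smaller.

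It may be tempting to conclude that the finished model will underpredict rapid decline by such an amount. The documents do not support that: they give no rates of drop-out, death or kidney failure, and nothing shows that exit related to the latent slope dominates. Confidence is high on the wording error and limited on the size of any bias in these cohorts.

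**What to change.** Reword the sentence to say that the mixed model is valid if values are missing at random given the included covariates and the observed eGFR, and that exit depending on the unobserved trajectory could bias slopes and rapid-decline probabilities.

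Add a sensitivity analysis for outcome-dependent exit, for example a shared-parameter joint model of eGFR and time to death, renal replacement or drop-out, where the cohorts recorded those times. Report how the slopes and rapid-decline probabilities change against the main model, and tabulate exit by reason.

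The rewording costs one sentence. The sensitivity analysis costs one extra model and somewhat more work. That work is not trivial with 13 predictors, time interactions and nested country and person effects, and it depends on event times whose availability the article does not document.
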